### Hypotheses

Patients in the EMDR group will show a reduction in the level and severity of substance use-related symptoms as compared to the TAU group.Patients in the EMDR group will show a reduction in the number of relapses as compared to the TAU group.Patients in the EMDR group will show a reduction in the severity of trauma-related symptoms as compared to the TAU group.There will be a reduction in depressive symptoms associated with a comorbid psychiatric disorder in the EMDR group as compared to the TAU group.There will be a reduction in (hypo) manic symptoms associated with a comorbid psychiatric disorder in the EMDR group as compared to the TAU group.There will be a reduction in general psychopathology symptoms associated with psychiatric comorbidity in the EMDR group as compared to the TAU group.Patients in the EMDR group will show an improvement in functioning as compared to the TAU group.

### Study Participants

The study sample will consist of 142 outpatients fulfilling the criteria of the Diagnostic and Statistical Manual of Mental Disorders, fifth edition (DSM-5), for SUD based on a clinical interview (Psychiatric Research Interview for Substance and Mental Disorders; PRISM) (42) and a review of case notes.

Inclusion criteria are: (1) aged 18–65, (2) outpatient, and (3) presence of one or more traumatic events currently causing trauma-associated symptoms (Impact of Events Scale-Revised, IES-R > 0) and Subjective Disturbance Unit (SUD) > 5, that assesses subjective disturbance in a scale between 0 and 10, but it is not necessary that traumatic events meet DSM-5 criteria for PTSD.

Exclusion criteria are: (1) presence of organic brain diseases, (2) presence of acute suicidal ideation, (3) having received a trauma-focused therapy or attended psychotherapeutic groups for survivors of violence within the last 2 years, or (4) acute episode of comorbid psychiatric disorder.

### Randomization Procedure

Clinical trials use randomization to balance confounding factors (to an uncontrolled extent) and to conceal allocation. However, complete randomization in small to moderate studies may fail to balance groups, severely affecting inference. To overcome this issue Efron (43) introduced the biased coin methods, which randomize each patient to one or the other group with a probability or another with the aim of increasing the balance of known confounding factors. Importantly, these methods still randomize each of the patients, thus balancing the unknown confounding factors (to the uncontrolled extend that complete randomization does) and concealing allocation (44). Non-deterministic dynamic allocation designs, such as the biased coin methods, were included in international guidelines for drug clinical trials (45) adopted by the European Community, Japan, United States FDA, Canada and Switzerland (Implementation of E9 Statistical Principles for Clinical Trials. URL: https://www.ich.org/products/guidelines/efficacy/efficacy-single/article/statistical-principles-for-clinical-trials.html).

In this trial, all patients meeting the inclusion criteria will receive the baseline (T0) assessment. After T0, participants will be assigned to the EMDR or TAU group following a biased coin procedure (46): (1) the first two patients will be randomly allocated to EMDR with *p* = 0.5, (2) the next patient will be allocated as follows: (b1) if one group already includes at least two more patients than the other group, the patient will be randomly allocated to EMDR with *p* = 0.8 is this is the smallest group and with *p* = 0.2 if it is the largest group, (b2) otherwise, we will first simulate that the patient is allocated to EMDR and calculate the sum of the between-group square standardized differences in site, age, sex, diagnosis (dual vs. not dual) and number of substances consumed during the month before the randomization (none. one or more than one), we will then simulate that the patient is allocated to TAU and recalculate the sum, and finally randomly allocate the patient to EMDR with *p* = 0.8 if this was associated to the smallest sum and with *p* = 0.2 if not. For example, if we had already included 10 patients to the EMDR group and 8 patients to the TAU group, the 19th patient would be randomly allocated with *p* = 0.2 for EMDR and *p* = 0.8 for TAU. If he/she was allocated to TAU, for the 20th patient we would calculate the above sum of covariates after simulating that the he/she is allocated to EMDR and after simulating that he/she is allocated to TAU, and if the sum of the EMDR simulation was larger than the sum of the TAU simulation, we would randomly allocate the 20th patient with *p* = 0.2 for EMDR and *p* = 0.8 for TAU. Following this procedure, the final groups should be balanced in size and matched in site, age, sex and diagnosis. All steps of the randomization process will be automatically carried out by an independent researcher in a central location using a computer program.

### Computation of Sample Size

The study aims to assess the efficacy of EMDR therapy compared with TAU, in inpatients with SUD, in terms of a reduction in substance use, a reduction in symptoms associated with craving and associated symptoms of anxiety and depression, and an improvement in functioning.

We aim for the study to be able to detect medium-sized differences in the pre-post changes between groups with an 80% statistical power. Given that there are no previous studies that report the variability of these changes, we have defined medium-sized differences as those with a medium effect size (*d* = 0.5). With the function power.t.test from R (http://www.r-project.org/), we have calculated that the number of patients required to detect medium-sized differences (*d* = 0.5) with a statistical power of 80% is *n* = 64 per intervention group (two groups, total *n* = 128). Assuming a loss percentage of approximately 10% of the patients in the study, it would be necessary to recruit approximately 142 patients, 71 for each intervention branch.

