## Abstract

**Background:** Psychological trauma has a strong negative impact on the onset, course and prognosis of substance use disorders (SUD). Few trauma-oriented treatment approaches have been trialed, but preliminary evidence exists of the efficacy of Eye Movement Desensitization and Reprocessing (EMDR) therapy in improving clinical symptoms in SUD patients.

**Objective:** To assess if EMDR therapy leads to: (1) reduced substance consumption; (2) an improvement in psychopathological and in trauma-related symptoms; and (3) an improvement in overall functioning. Our hypothesis is that the EMDR group will improve in all variables when compared to the treatment as usual (TAU) group at 6 and 12-months visits.

**Method:** In this multicenter phase II rater-blinded randomized controlled trial, 142 SUD patients with a history of psychological trauma will be randomly assigned to EMDR (*n* = 71) or to TAU (*n* = 71). Patients in the EMDR group will receive 20 psychotherapeutic sessions of 60 min over 6 months. Substance use will be measured using the Timeline Followback Questionnaire, the Dependence Severity Scale and the Visual Analog Scale. Traumatic events will be measured by The Holmes-Rahe Life Stress Inventory, the Childhood Trauma Questionnaire Scale, the Global Assessment of Posttraumatic Stress Questionnaire, the Impact of Event Scale-Revised and the Dissociative Experiences Scale. Clinical symptomatology will be evaluated using the Hamilton Depression Rating Scale, the Young Mania Rating Scale and the Brief Psychiatric Rating Scale. Functionality will be assessed with the Functioning Assessment Short Test. All variables will be measured at baseline, post-treatment and 12 months as follow-up. Primary outcome: to test the efficacy of EMDR therapy in reducing the severity of substance use. The secondary outcomes: to test the efficacy in reducing trauma-related psychological symptoms and psychopathological symptoms and in improving overall functioning in patients with comorbid SUD and a history of psychological trauma.

**Conclusion:** This study will provide evidence of whether EMDR therapy is effective in reducing addiction-related, trauma and clinical symptoms and in improving functionality in patients with SUD and a history of trauma.

**Clinical Trial Registration:** The trial is registered at ClinicalTrials.gov, identifier: NCT03517592.

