### Study Outcomes

The primary outcome is to test the efficacy of EMDR therapy in reducing the severity of substance use in patients with comorbid SUD and a history of psychological trauma, irrespective of whether the patient meets DSM-V PTSD criteria. Changes from baseline in the severity of substance use are measured by the Timeline Follow Back (TLFB) (31), the Severity of Dependence Scale (SDS) (32), and the Visual Analog Scale (VAS).

The secondary outcome is to test the efficacy of EMDR in improving trauma-related psychological symptoms, psychopathological symptoms, and the overall functionality in SUD patients with a history of psychological trauma. Changes in psychological trauma and dissociative symptoms are measured using the Global Assessment of Posttraumatic Stress Questionnaire (EGEP-5) (33), the Impact of Event Scale-Revised (IES-R) (34), and the Dissociative Experiences Scale (DES) (35), respectively. The type and severity of traumatic experiences are measured using the Childhood Trauma Questionnaire (CTQ) (36) and The Holmes-Rahe Life Stress Inventory (37). Changes in psychopathological symptoms are measured by the Hamilton Depression Rating Scale (HDRS) (38), Young Mania Rating Scale (YMRS) (39), and the Brief Psychiatric Rating Scale (BPRS) (40). Changes in overall functioning will be measured using the Functioning Assessment Short Test (FAST) (41).

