### Statistical Analysis

The distribution of socio-demographic and clinical characteristics between groups in the baseline state will be summarized using descriptive statistics. The change in clinical and functional variables with regard to baseline evaluation at strategic points of the intervention will be analyzed using mixed-effects repeated-measures linear models, including as fixed factors time, treatment conditions and their interactions, and as a random factor the site. The differences between groups, for the categorical variables and main clinics, will be analyzed by adding covariates to the models. Those covariates that are statistically significant may be added in the same model to determine which covariates are best predictors of the response. The size of the effects will be estimated using the g of Hedges or the r of Pearson. It will be corrected for multiple comparisons. The statistical software used for the analysis will be the latest available version of R. We will conduct an intention to treat (ITT) analysis. The “Last Observation Carried Forward” (LOCF) method will be used for losses of follow-up.

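### The stated 80% power holds for one uncorrected t-test; under the promised multiplicity correction, power for each of the three unranked primary measures is lower, about 66% with Bonferroni

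*Protocol article*

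**What the plan says.** - **Sample size.** Computation of Sample Size sets the target: "We aim for the study to be able to detect medium-sized differences in the pre-post changes between groups with an 80% statistical power". It takes a medium effect, d = 0.5, because no earlier study reports the variability of these changes. The calculation is introduced by "With the function power.t.test from R", and the result is given "with a statistical power of 80% is *n* = 64 per intervention group", or 128 in total. This is raised to about 142 (71 per arm) for roughly 10% losses. The section states no alpha, names no outcome or visit for the test, and makes no allowance for multiple tests. Its opening sentence lists several targets: substance use, craving, anxiety and depression, and functioning.
- **Primary outcome.** Study Outcomes says "Changes from baseline in the severity of substance use are measured by the Timeline Follow Back (TLFB" and then adds the SDS and the VAS. None of the three is ranked above the others. Instruments and Measures shows that they capture different things: daily use, degree of dependence, and intensity of craving.
- **Hypothesis.** The Abstract expects that "the EMDR group will improve in all variables when compared to the treatment as usual (TAU) group at 6 and 12-months visits".
- **Multiplicity.** Statistical Analysis promises: "It will be corrected for multiple comparisons". It gives no method, no family of tests and no rule for declaring success.

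**The concern.** These statements do not fit together. The sample size describes one test at a full 5% level. The outcome section offers three tests of equal standing, and the analysis section says the tests will be corrected. At 64 per arm the single-test power is only just 80%, so any lower threshold takes that comparison under 80%.

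Two things are at stake. A reader who takes 80% as the power for each primary measure is misled. And a mixed result, for example less craving but no fewer days of use, has no pre-set reading, which leaves room to choose the interpretation after the data are seen. This matters because the Introduction presents the choice of addiction outcomes as primary as one of the trial's novel features.

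**Working it through.** **Inputs**
- From Computation of Sample Size: d = 0.5 on the between-group difference in pre-post change; one two-sample t-test; 64 evaluable per arm; 71 per arm recruited.
- From Study Outcomes: three primary measures, unranked.
- Inferred: two-sided alpha of 0.05.
- Assumed, because the document does not give them: the correction method (Bonferroni or Holm), d = 0.5 on every measure where rules combine measures, and equal correlations between measures from 0 to 0.9.

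**1. Reproduce the plan's figure.** Power = P(|T| > t(1 − α/2; 2n − 2)), where T is noncentral t with noncentrality d·√(n/2). With n = 64, the noncentrality is 0.5 × √32 = 2.828, there are 126 degrees of freedom, and the critical value at α = 0.05 is 1.979. Power is 80.15%. Solving for 80% gives n = 63.77, so 64. A one-sided 0.05 test would need only 51, so it does not fit. The dropout step also agrees: 128 / 0.9 = 142.2.

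**2. Bonferroni over three.** α = 0.05 / 3 = 0.01667, critical value 2.426.
- Power per measure at 64 per arm: 65.6%.
- Power per measure if all 71 per arm are analysed: 71.0%.
- Effect detectable with 80% power at 64 per arm: d = 0.58.
- Sample size for 80% per measure: 86 per arm, 172 evaluable; 172 / 0.9 = 191.1, so 192 recruited.

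**3. Rules that combine the three measures** (64 per arm, simulated; the zero-correlation values for the second and third rows can be checked by hand).

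| Rule | Correlation 0 | 0.5 | 0.9 |
|---|---|---|---|
| Holm, average power per measure | 75% | 73.5% | 71.5% |
| All three significant at uncorrected 0.05 | 52% | 61% | 72% |
| At least one significant, Bonferroni | 96% | 87% | 75% |

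Hand checks at zero correlation: all three, 0.8015³ = 0.515; at least one, 1 − (1 − 0.656)³ = 0.959. A normal approximation in place of the t-distribution raises the lower ends by about a point (for example, 0.807³ = 0.526).

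**4. Fixed testing order.** The first test uses the full 0.05 and keeps 80.15%. Later tests are made only if the earlier ones succeed.

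**5. If the 12-month contrasts are also co-primary** (an assumption resting on the Abstract): six tests, α = 0.05 / 6 = 0.00833, critical value 2.681. Bonferroni power per test is 56.0%.

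**The case against.** The strongest reply is that nothing in the sample size section is miscalculated. The 64 per arm is right for the test it describes, and 142 is right for the loss assumed. That stands: this is a point about multiplicity and power, not an arithmetic error.

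It also stands that the correction's method and family may be set out in an analysis plan that is not shown. The protocol's sentence on correction follows sentences on covariates and effect sizes and could be aimed elsewhere. A reader might therefore infer that the trial simply does not have 80% power. The document does not support so flat a statement. With an any-one-measure rule under Bonferroni, power is above 80% up to a correlation of about 0.7, if d = 0.5 holds on all three measures. A fixed order keeps 80% for the first test. But the protocol states neither rule. A fixed order would mean ranking measures that it leaves unranked, and an any-one rule sits poorly with a hypothesis of improvement throughout.

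Three other stronger readings should be resisted:
- **Six co-primary tests.** Methods calls 6 months post-treatment and 12 months follow-up, and the Discussion gives the later visit the role of checking whether gains last. The six-test figure rests on one Abstract sentence.
- **All measures must succeed.** That same sentence is a directional hypothesis that also covers secondary outcomes. It is not a success criterion.
- **An inflated false-positive rate.** Three independent uncorrected tests would give 1 − 0.95³ = 14.3%, but the protocol promises a correction. That harm would arise only if the correction were dropped or did not cover these measures.

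Finally, the planned repeated-measures mixed model might be more precise than a t-test. The sample size section claims no such gain, and the document gives no correlation from which to work one out.

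**Conclusion.** The concern holds in a conditional form. The 64 per arm gives 80% power for one uncorrected test, with two-sided 0.05 inferred. If each of TLFB, SDS and VAS must pass a corrected threshold, power per measure at d = 0.5 is below 80%. It is about 66% with Bonferroni over three, or about 72% to 75% on average with Holm if the effect is the same on all three. If all three must succeed without correction, it is about 52% to 72% over correlations of 0 to 0.9.

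The exact shortfall depends on a method, family and success rule that the protocol does not give. The direction does not change under any of these readings. An analysis plan applying Bonferroni or Holm across the three measures would leave the printed 80% wrong for each measure. Only a ranking, or an any-one-measure rule with correlations that are not very high, would rescue it.

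**What to change.** Preferred: in Study Outcomes, name one primary measure at one visit, for example TLFB use-days at T2 (6 months), tested at two-sided 5%. State that alpha, measure and visit in Computation of Sample Size. In Statistical Analysis, test SDS, VAS and the 12-month contrasts only after the primary succeeds, in a fixed sequence or with Holm. The 64 per arm and 80% then hold as printed.

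Alternative: keep three co-equal primaries, state the success rule and the correction, and restate the power to match. With Bonferroni that is about 66% per measure at 64 per arm, or a detectable d of 0.58.

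Either route changes wording in three sections and adds no patients. The cost is that two measures become key secondary outcomes, or that a less favourable power figure is printed. Keeping 80% per measure under Bonferroni over three would instead need about 192 recruited rather than 142. The choice should be recorded before anyone sees outcome data by arm.

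### The 80% power at 64 per arm holds for one uncorrected test, but the plan has three unranked primary measures and promises a multiple-comparison correction that the sizing does not allow for

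*Protocol article*

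**What the plan says.** **Sizing.** Under Computation of Sample Size, the protocol article sets out "to detect medium-sized differences in the pre-post changes between groups with an 80% statistical power". The tool is given ("With the function power.t.test from R"), and so is the standardised effect, d = 0.5. The result is 64 patients "per intervention group (two groups, total *n* = 128"). Recruitment is then raised to 142, 71 per arm: "Assuming a loss percentage of approximately 10% of the patients in the study". The section states no alpha, names no single outcome for the calculation, and mentions no allowance for several tests.

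**Primary outcome.** Study Outcomes gives three instruments for the primary outcome, on which changes since entry "are measured by the Timeline Follow Back (TLFB) (31), the Severity of Dependence Scale (SDS) (32), and the Visual Analog Scale (VAS"). None is ranked above the others, and they are not combined.

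**Analysis.** Statistical Analysis says "It will be corrected for multiple comparisons". It plans mixed-effects repeated-measures models, an intention-to-treat analysis, and LOCF for losses to follow-up.

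**Visits.** The hypothesis in the Abstract is that "the EMDR group will improve in all variables when compared to the treatment as usual (TAU) group at 6 and 12-months visits". Methods calls 6 months post-treatment and 12 months follow-up.

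**The concern.** A power statement describes the test that will be carried out. Here the sizing describes one test at the full 0.05, while the analysis describes several primary tests with a correction. Most corrections over three equal measures lower the threshold that each measure must pass, so the power for each measure falls below the figure the article gives.

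The three instruments are not interchangeable. By the article's own description, TLFB records daily use, SDS the degree of dependence and VAS craving. A result on one does not answer the question for the others, so power per measure is the relevant quantity.

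If this stays as it is, a negative result on a primary measure would be read against 80% power that the design may not have. Dropping the correction is no remedy: with three independent tests at 0.05, the chance of at least one false positive is 1 − 0.95³ = 14.3%.

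**Working it through.** **Inputs from the article:** d = 0.5 on pre-post change; power 80%; 64 analysed per arm; 1:1 allocation; about 10% loss; three primary measures; a correction of unnamed method and family. **Inferred:** two-sided alpha 0.05.

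**Step 1: reproduce the plan's figure.** For a two-sample t-test with n per arm, power = P(T′ > t(1−α/2; 2n−2)), where T′ is noncentral t with noncentrality d·√(n/2).

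- Two-sided 0.05, d = 0.5, 80%: n = 63.77, so 64 per arm. At n = 64 the noncentrality is 0.5 × √32 = 2.83 and power is 80.1%.
- One-sided 0.05 gives 50.15, so 51 per arm: no match.
- Two-sided 0.05/3 gives 85.2, so 86 per arm: no match.
- Loss: 128/0.9 = 142.2 and 64/0.9 = 71.1, consistent with 142 and 71.

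So the figure rests on one uncorrected test at two-sided 0.05 (or the equivalent one-sided 0.025).

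**Step 2: same formula, Bonferroni over three measures** (0.05/3 = 0.0167).

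- 64 per arm: 65.6%. Hand check by normal approximation: Φ(2.83 − 2.39) = Φ(0.43), about 67%.
- Effect detectable with 80% power at 64 per arm: d = 0.58.
- 71 per arm (everyone randomised, through ITT with LOCF): 71.0%, against 84.1% uncorrected.

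**Step 3: Holm over three measures,** by simulation, correlation between measures 0 to 0.7.

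| Analysed per arm | All three effects d = 0.5 | Only one effect real |
|---|---|---|
| 64 | about 74–76% | about 66% |
| 71 | about 79–81% | about 71% |

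The all-effects column uses a normal approximation; with t statistics it is about one percentage point lower. The 71-per-arm row assumes that LOCF does not dilute the effect.

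**Step 4: a wider family, for range only.** If the three measures at both 6 and 12 months formed one Bonferroni family of six (0.05/6 = 0.0083), power would be 56.0% at 64 per arm and 61.9% at 71. The protocol does not say that the visits share a family.

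**Step 5: cost of keeping 80% under Bonferroni over three.** 86 per arm, 172 in total, and 172/0.9 = 191.1, so 192 recruited. This is shown for scale; the fix does not need it.

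**The case against.** The strongest reply is that the article names neither the method nor the family of the correction. Those details are commonly left to an analysis plan, so their absence is no fault. A reader might infer that true power is 66% or less, or that the trial cannot reach 80% for any given primary measure. The documents do not support either reading. Holm at 64 per arm does better than 66% if all three effects are real. With 71 per arm it comes to about 80%. A fixed testing order would keep 80% for the first measure. Much lower figures need a family that pools both visits, or primary with secondary scales, and no section states one. The Abstract's sentence on 6 and 12 months is a hypothesis, not a testing rule.

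Two more points are fair. The planned analysis is a repeated-measures mixed model with a 3-month visit for the substance measures; its power was not computed and may differ from that of a t-test. And the chance that at least one of three measures passes Bonferroni is about 83–96% if all three effects are d = 0.5 (correlation 0.7 down to 0).

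These points set the size of the problem but do not remove it. The commitment to correct and the 80% figure are both already in the article, and the second ignores the first. The sizing itself treats 64, not 71, as the analysed number, and carrying baseline forward for early losses records no change, which tends to shrink a treatment difference. The article does not claim power for at least one of three. An analysis plan could secure the 80% at 64 per arm by ranking or narrowing the primary outcome, which is the change proposed here.

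**Conclusion.** The point holds as an inconsistency between sizing and analysis. It is not an arithmetic error: 64, 128 and 142 all reproduce. The 80% is true of one uncorrected two-sided 0.05 test and is not secured for each of three equal primary measures under the promised correction. At the plan's own 64 per arm the shortfall is about 4 to 14 percentage points: 80.1% against 74–76% (Holm, all effects real) or 65.6% (Bonferroni, or approximately Holm with one real effect). With 71 analysed it ranges from none to about 9 points (79–81% to 71.0%).

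This rests on the inferred alpha of 0.05, a t-test on pre-post change, a family of exactly three tests and, for the figures at 71, undiluted LOCF values.

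**What to change.** Choose one of two wordings, and state alpha in either case.

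**(a) Preferred.** Name one primary measure at one visit and test it first at two-sided 0.05, so that the 80% statement is true for that test. TLFB change at 6 months is a reasonable choice because reduced consumption is the first objective in the Abstract, but the sample-size section does not name it, so this is a decision for the sponsor. Then test the other two measures and the 12-month comparisons in a fixed order, each at 0.05 only if the one before succeeds. Correct the secondary scales in a separate family.

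**(b)** Keep three equal measures and replace the 80% in the sample-size section with: about 66% per measure for d = 0.5 at 0.05/3; 80% for d = 0.58.

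Both are wording changes with no extra patients, to be settled before unblinding. The price of (a) is that later measures are confirmatory only if the first succeeds; the price of (b) is a less favourable power statement.
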